## 1. Introduction

This document is the Statistical Analysis Plan (SAP) for the PREDNOS 2 trial, and should be read in conjunction with the current trial protocol. This SAP details the proposed analyses and presentation of the data for the main paper(s) reporting the results for PREDNOS 2.

The results reported in these papers will follow the strategy set out here. Subsequent analyses of a more exploratory nature will not be bound by this strategy, though they are expected to follow the broad principles laid down here. The principles are not intended to curtail exploratory analysis (e.g. to decide cut-points for categorisation of continuous variables), nor to prohibit accepted practices (e.g. transformation of data prior to analysis), but they are intended to establish rules that will be followed, as closely as possible, when analysing and reporting data.

Any deviations from this SAP will be described and justified in the final report or publication of the trial (using a table as shown in Appendix A). The analysis will be carried out by an appropriately qualified statistician, who should ensure integrity of the data during their data cleaning processes.

## 2. Background and rationale

The background and rationale for the trial are outlined in detail in the protocol. In brief, presenting episodes and relapses of nephrotic syndrome in children with steroid sensitive nephrotic syndrome (SSNS) are treated with high dose prednisolone. At least 50% of relapses are precipitated by viral upper respiratory tract infection (URTI), possibly mediated through release of cytokines. Furthermore, in children with frequently relapsing SSNS, the development of an URTI results in relapse in over 50% of instances. Given these strong links between viral URTI and relapse, and the morbidity and cost associated with relapse and its treatment, it is logical that attempts are made to ameliorate the URTI-driven process.

## 3. Trial objectives

The primary objective is to determine whether a six day course of oral prednisolone given at the time of URTI reduces the incidence of first URTI-related relapse in children with relapsing SSNS.

Secondary objectives are to determine whether a six day course of oral prednisolone given at the time of URTI:

- i. Reduces the overall rate of URTI-related relapse of nephrotic syndrome
- ii. Reduces the overall rate of (URTI-related and non URTI-related) relapse of nephrotic syndrome
- iii. Reduces the cumulative dose of prednisolone received over the 12 month trial period
- iv. Reduces the incidence and prevalence of adverse effects of prednisolone including behavioural abnormalities
- v. Reduces the number of subjects undergoing escalation of background immunosuppressive therapy

|                                                                                                                                                                                                                                                                                                                                                                                                                                                                                                                                                                                                                                                                                                                      |
|----------------------------------------------------------------------------------------------------------------------------------------------------------------------------------------------------------------------------------------------------------------------------------------------------------------------------------------------------------------------------------------------------------------------------------------------------------------------------------------------------------------------------------------------------------------------------------------------------------------------------------------------------------------------------------------------------------------------|
| vi. Increases the number of subjects undergoing reduction of background immunosuppressive therapy                                                                                                                                                                                                                                                                                                                                                                                                                                                                                                                                                                                                                    |
| vii. Is more cost-effective than standard therapy                                                                                                                                                                                                                                                                                                                                                                                                                                                                                                                                                                                                                                                                    |
| 4. Trial methods                                                                                                                                                                                                                                                                                                                                                                                                                                                                                                                                                                                                                                                                                              |
| 4.1. Trial design                                                                                                                                                                                                                                                                                                                                                                                                                                                                                                                                                                                                                                                                                             |
| 
PREDNOS 2 is a multi-centre, prospective, double-blind, superiority, parallel group, phase III randomised controlled trial. See Appendix B for trial schema.
 
Participants will be recruited from secondary care.
                                                                                                                                                                                                                                                                                                                                                                                                                                                                                       |
| 4.2. Trial interventions                                                                                                                                                                                                                                                                                                                                                                                                                                                                                                                                                                                                                                                                                      |
| 
Active treatment group: Daily prednisolone for a total of 6 days commenced within 24 hours of the criteria for an URTI being met.
 
Control group: Daily matched placebo for a total of 6 days commenced within 24 hours of the criteria for an URTI have being met.
 
See protocol for detailed information on the dosing of the study drug.
                                                                                                                                                                                                                                                                                                                                                       |
| 4.3. Primary outcome measure                                                                                                                                                                                                                                                                                                                                                                                                                                                                                                                                                                                                                                                                                  |
| 
The primary outcome is first URTI-related relapse of nephrotic syndrome during the 12 month follow up period.
 
Relapse is defined as Albustix positive proteinuria (+++ or greater) for 3 consecutive days or the presence of generalised oedema plus 3+ proteinuria.
 
An URTI-related relapse is defined as a relapse occurring within 14 days of the development of an URTI.
                                                                                                                                                                                                                                                                                                                    |
| 4.4. Secondary outcome measures                                                                                                                                                                                                                                                                                                                                                                                                                                                                                                                                                                                                                                                                               |
| 
The secondary outcomes are as follows:
 
 
i. Rate of URTI-related relapse of nephrotic syndrome
 
ii. Rate of relapse (URTJ-related and non URTI-related) of nephrotic syndrome
 
iii. Cumulative dose of prednisolone (mg/kg and mg/m^2) received over the 12 month period
 
iv. Incidence of serious adverse events (SAEs)
 
v. Incidence of adverse effects of prednisolone including assessment of behaviour using the Achenbach Child Behaviour Checklist
 
vi. Incidence of escalation of background immunosuppressive therapy
 
vii. Incidence of reduction of background immunosuppressive therapy
 
 |

- viii. Quality of life using the PedsQL (0=worst, 100=best). See Section 9.4 for questionnaire scoring.
- ix. Cost per relapse of nephrotic syndrome
- x. Cost per QALY gained

The secondary outcomes measures ix and x relate to the health economic analysis and are not part of this SAP.

#### **4.5. Timing of outcome assessments**

The schedule of trial procedures and outcome assessments are given in the protocol section 4.12.

#### **4.6. Randomisation**

Participants will be randomised in a 1:1 ratio to either active treatment or placebo.

Randomisation will be performed centrally at the Birmingham Clinical Trials Unit (BCTU) using a minimisation algorithm incorporating the following factor:

- Treatment regimen subject is receiving at randomisation: no background immunosuppressive therapy; long term maintenance prednisolone therapy; long term maintenance prednisolone therapy plus other immunosuppressive therapies; other immunosuppressive therapies alone.

#### **4.7. Sample size**

A total of 360 subjects will be recruited into the trial (180 into each group).

In children with frequently relapsing SSNS, the development of an URTI results in relapse in around 50% of instances. To detect an absolute difference of 17.5% (i.e. 35% proportional reduction) in URTI-related relapse rate (i.e. from 50% to 32.5%), with 80% power and  $\alpha=0.05$ , requires 250 subjects in total. Allowing for 30% drop out (e.g. subject withdrawal or lost to follow up, or subject not having an URTI during the 12 month follow up period), will require recruitment of 360 subjects. We therefore propose to recruit 360 subjects, 180 to each group.

#### **4.8. Framework**

The objective of the trial is to test the superiority of one intervention to another.

The null hypothesis is that there is no difference in the number of children experiencing an URTI-related relapse between the intervention groups. The alternative hypothesis is that there is a difference between the groups.

## **4.9. Interim analyses and stopping guidance**

A separate Data Monitoring Committee (DMC) reporting template will be drafted and agreed by the DMC including an agreement on which outcomes will be reported at interim analyses. The statistical methods stated in this SAP will be followed for the outcomes included in the DMC report, where possible.

Interim analyses of efficacy and safety are planned annually. The Haybittle-Peto approach will be used whereby all interim analyses use a difference of 3 standard errors (approximately  $p=0.002$ ) as a stopping guideline. These interim analyses will be reviewed by the DMC on an annual basis or more frequently if required by the DMC or Trial Management Committee

## **4.10. Internal Pilot Progression Rules**

Not Applicable.

## **4.11. Timing of final analysis**

The final analysis for the trial will occur after the last patient randomised into the trial has reached 12 months follow up and the corresponding outcome data has been entered onto the trial database and validated as being ready for analysis. This is provided that the trial has not been stopped early for any reason (e.g. DMC advice or funding body request).

## **4.12. Timing of other analyses**

Not Applicable.

## **4.13. Trial comparisons**

All references in this document to 'group' refer to the active 6 day daily course of prednisolone group or to the placebo group.

# **5. Statistical Principles**

## **5.1. Confidence intervals and p-values**

All estimates of differences between groups will be presented with two-sided 95% confidence intervals, unless otherwise stated. P-values will be reported from two-sided tests at the 5% significance level.

## **5.2. Adjustments for multiplicity**

No correction for multiple testing will be made.

## **5.3. Analysis populations**

All primary analyses (primary and secondary outcomes including safety outcomes) will be based on the intention-to-treat (ITT) principle. Participants will be analysed in the intervention group to which they were randomised, and all participants shall be included whether or not they

received the allocated intervention following an URTI. This is to avoid any potential bias in the analysis.

The ITT population will not include all of the randomised population. Analyses will be based on a modified ITT population which will include only those participants who had an URTI over the 12 month follow up period. Excluding those participants who did not have an URTI will result in no bias as taking the study medication is conditional on them experiencing an URTI, and this should by chance be balanced between the two groups.

#### **5.4. Definition of adherence**

Adherence to allocated intervention will be monitored using the parent-reported tablet count. This is instead of using the returned pot tablet count because the tablet count is just a check of what they have taken compared to what they have said they have taken, rather than whether or not they have been adherent to the intervention. This is further complicated by reissued pots, pots that have not been returned, dropped tablets etc. Good adherence is defined as participants taking 80-120% of their required tablets.

#### **5.5. Handling protocol deviations**

A protocol deviation is defined as a failure to adhere to the protocol such as errors in applying the inclusion/exclusion criteria, the incorrect intervention being given, incorrect data being collected or measured, follow-up visits outside the visit window or missed follow-up visits. We will apply a strict definition of the ITT principle and will include all participants as per the modified ITT population described in section 5.3 for the primary analyses, in some form, regardless of deviation from the protocol. This includes participants who were randomised but later found to not meet the inclusion or exclusion criteria. This does not include those participants who have specifically withdrawn consent for the use of their data in the first instance; however these outcomes will be explored as per other missing responses.

#### **5.6. Unblinding**

This is a double-blind trial with the participants and clinicians remaining blind to treatment allocation. To maintain blinding, participants randomised to the control group receive the same number of study tablets that they would have received in the active treatment group through supplemental placebo tablets. The Trial Statistician has been unblinded to the intervention code for all of the interim analyses, and presented unblinded analyses to the DMC.

### **6. Trial population**

#### **6.1. Recruitment**

A flow diagram (as recommended by CONSORT) will be produced to describe the participant flow through each stage of the trial. This will include information on the number (with reasons) of losses to follow-up (drop-outs and withdrawals) over the course of the trial.

## **6.2. Baseline characteristics**

The trial population will be tabulated with categorical data summarised by number of participants, counts and percentages, and continuous data summarised by the number of participants, mean and standard deviation if deemed to be normally distributed or number of participants, median and interquartile range if data appear skewed, and ranges if appropriate. Tests of statistical significance will not be undertaken, nor confidence intervals presented.

## **7. Intervention(s)**

### **7.1. Description of the intervention(s)**

Not Applicable.

### **7.2. Adherence to allocated intervention**

Adherence to allocated intervention will be summarised descriptively. At each follow-up visit, if the participant had an URTI the following questions are completed:

- Did the parent commence their child on study medication at time of URTI?
- If study medication not commenced, please state reason
- Date study medication commenced (note: study medication should be commenced within 24 hours of the criteria for an URTI being met).
- Was the whole 6 day course of study medication taken?
- If no, how many days were missed?
- Was the 6 day course prematurely discontinued?
- If study medication discontinued, please state reason

These questions will be summarised and presented by group.

## **8. Protocol deviations**

Frequencies and percentages by group will be tabulated for the protocol deviations.

## **9. Analysis methods**

### **9.1. Covariate adjustment**

In the first instance, intervention effects between groups for all outcomes will be adjusted for the minimisation parameter listed in section 4.6. Other covariate adjustment will be baseline values for parameters where available (e.g. an analysis of questionnaire scores will also include the baseline score as a covariate in the model).

If covariate adjustment is not possible (e.g. the model does not converge), the minimisation variable covariate will be removed from the model, but where applicable adjustment for baseline values will still be made. If the model still does not converge, unadjusted estimates will be produced, and it will be made clear in the final report why this occurred (e.g. not possible due to low event rate/lack of model convergence).

If the log-binomial model fails to converge, a Poisson regression model with robust standard errors will be used to estimate the same parameters. If this also fails to converge, unadjusted estimates will be produced from the log-binomial model. It will be made clear in the final report why this occurred (e.g. not possible due to low event rate/lack of model convergence).

## **9.2. Distributional assumptions and outlying responses**

Distributional assumptions (e.g. normality of regression residuals for continuous outcomes) will be assessed visually prior to analysis; although in the first instance the proposed primary method of estimation in this analysis plan will be followed. If responses are considered to be particularly skewed and/or distributional assumptions violated, the impact of this will be examined through sensitivity analysis; this will consist of transformation of responses prior to analysis (e.g. log transformation) in the first instance. If extreme values are apparent and considered to be affecting the integrity of the analysis, a sensitivity analysis consisting of removing the outlying response(s) and repeating the analysis will be performed. Output from these analyses, if performed, will be described and presented alongside the original analysis (or included, e.g. in appendices) with the excluded values clearly labelled.

## **9.3. Handling missing data**

In the first instance, analysis will be completed on received data only with every effort made to follow-up participants even after protocol violation to minimise any potential for bias. To examine the possible impact of missing data on the results, and to make sure we are complying with the intention-to-treat principle, sensitivity analysis will be performed on the primary outcome measure. See section 9.10 for further details regarding sensitivity analyses.

## **9.4. Data manipulations**

The Trial Statistician will derive all responses from the raw data recorded in the database:

### **Cumulative dose of prednisolone:**

Prednisolone is recorded in both Part B1 and Part I of the follow-up form at each time-point. Part I dosing is recorded as free text so in order to use this data for the cumulative prednisolone doses, the Trial Statistician will recode all the free text as the numerical variables: dose and frequency where possible.

Then, in the first instance, clean data from Part B1 and Part I will be combined.

Data can then be checked across both parts of the form to see whether there are any duplicates in doses received. Duplicated doses will be deleted.

Any dosing regimens that are ongoing on one form will be checked against the following form for the stop date. Once a stop date has been obtained, the entry or entries where

the dose is ongoing will be collapsed, so that there is one dose regimen with a defined start and stop date.

There may be some instances where start date and/or stop date are missing as the sites had a rough idea of the treatment regimen but not of the dates e.g. tapering regimen following a relapse. In these cases it is more appropriate to check against the participants relapse history and received treatment in order to make sensible assumptions about the missing dates, than to not use the available data.

If a start date is pre-randomisation date, and the prednisolone regimen is on-going at point of randomisation, the start date will be replaced with the randomisation date so as to only capture prednisolone therapy during the trial.

Cumulative prednisolone dose will be based on those participants who complete the full 12 months trial follow-up. If the dose is ongoing at 12 months the dose will be truncated at 12 months (i.e. randomisation date + 12 months) to provide the cumulative prednisolone dose over the 12 month follow-up period.

For those in the active treatment group, the trial treatment will be included in the cumulative prednisolone. Where tablet count is available, the tablet count will be converted to mg, and then added to the cumulative prednisolone for that participant. If tablet count is not available, then other information on adherence to the trial medication will be used instead to provide an estimated tablet count or dose.

Since drug data is notoriously difficult to collect and analyse, as a check of the statistical code, a manual check and calculation of cumulative prednisolone for 20 participants will be undertaken.

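### Cumulative prednisolone dose is limited to 12-month completers and derived by an unblinded statistician, leaving secondary objective iii open to selection and assessor bias of unknown direction and size

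*Combined protocol and SAP*

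**What the plan says.** **Analysis set.** SAP 5.3 sets the general rule: "All primary analyses (primary and secondary outcomes including safety outcomes) will be based on the intention-to-treat (ITT) principle". It then defines the set: "Analyses will be based on a modified ITT population which will include only those participants who had an URTI over the 12 month follow up". Protocol 4.29 agrees: the only randomised children left out are those with no URTI. SAP 5.5 counts missed follow-up visits as protocol deviations and undertakes to keep the modified ITT children in the analysis in some form despite deviations. For cumulative dose, SAP 9.4 sets a different rule: "Cumulative prednisolone dose will be based on those participants who complete the full 12 months trial follow-up".

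**Model.** SAP 9.6 analyses cumulative dose as one 12-month total by linear regression. In the same section, the relapse rates get an offset for time in the trial. SAP 9.10 confines sensitivity analyses to the primary outcome.

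**Derivation.** SAP 9.4 opens with the statement that "The Trial Statistician will derive all responses from the raw data recorded in the database". For the dose records, "the Trial Statistician will recode all the free text as the numerical variables: dose and frequency where possible". Duplicates between the two parts of the form are deleted. Where start or stop dates are missing, relapse history and treatment received are used to "make sensible assumptions about the missing dates". Study tablets are then added in the active arm only.

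**Blinding.** SAP 5.6: "The Trial Statistician has been unblinded to the intervention code for all of the interim analyses". SAP 4.9 plans these analyses annually. No section gives the final dose derivation to someone who has not seen the code.

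**The concern.** Completing 12 months is a post-randomisation event, and it may be related to relapse and steroid exposure. Comparing completers only can therefore lose the balance that randomisation provides. It also throws away usable information: protocol 4.26 lets a family stop follow-up while agreeing that data already collected may be used in the final analysis, yet those records do not enter this outcome.

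Separately, reading free text, choosing which entry is a duplicate and assuming a date all involve judgement. When the person judging knows the arm, the result can drift without anyone intending it. A fixed algorithm or masking would prevent this, and the SAP provides neither.

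The outcome matters for interpretation. Protocol section 8 gives the hypothesis that the strategy lowers total prednisolone exposure, and protocol 7.1 names the opposite risk, more steroid without fewer relapses. Cumulative dose is the outcome that separates the two.

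**Working it through.** **1. The plan's own figures.** The documents give no SD, power or sample size for cumulative dose. The stated figures that can be checked are those for the primary outcome (protocol 4.28, SAP 4.7). Two proportions, 50% against 32.5%, two-sided alpha 0.05, power 80%, pooled variance without continuity correction, give 124 per arm, 248 in total (stated 250). With 30% loss, 250/0.70 = 358 (stated 360). Both reproduce within rounding.

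**2. How many children the completer rule could remove.** Inputs: 30% total allowance (protocol 4.28) and about 24% completing without an URTI up to 12 July 2016 (protocol 4.29).
- Children with an URTI: 360 × 0.76 = 273.6, about 274.
- Left after the full allowance: 360 × 0.70 = 252.
- Difference: about 22 children, or 1 − 0.70/0.76 = 7.9% of children with an URTI.

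This is a planning allowance, not observed loss, and the documents do not split it by arm.

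**3. Bias formula.** Let d be the share of non-completers in an arm and g their mean 12-month dose minus that of completers. The completers' mean is below the arm's mean by d × g. The error in the active-minus-control difference is d(control) × g(control) − d(active) × g(active).
- Equal d and equal g in both arms: error zero.
- Only control leavers informative, d = 8%, dose rate r times that of completers (r is an assumption):

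| r | Arm mean relative to completers, 0.92 + 0.08r | Shortfall, 1 − 1/mean |
|---|---|---|
| 1.25 | 1.02 | 2.0% |
| 1.5 | 1.04 | 3.8% |
| 2 | 1.08 | 7.4% |

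If only active leavers are informative, the error has the opposite sign.

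**4. The same in SD units (SD and arm-specific loss assumed).** With 360 × 0.70/2 = 126 per arm, SE = √(2/126) = 0.126 SD, and the difference detectable with 80% power is 0.35 SD.
- 8% loss, informative in one arm only, gap of 1 SD: error 0.08 SD.
- Loss of 5% against 15%, gap of 0.5 SD in both arms: (0.15 − 0.05) × 0.5 = 0.05 SD. The two-sided type I error, P(|Z + bias/SE| > 1.96), is 6.8%.
- The same loss with a gap of 1 SD: 0.10 SD and 12.5%. These last two cases average 10% loss, above the allowance in step 2, so they are stress cases.

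**5. Scale of one date assumption.** The alternate-day phase of the relapse regimen in protocol 4.9 is 14 doses of 40 mg/m² over four weeks. A two-week error in an assumed stop date is 7 × 40 = 280 mg/m². A full study course without maintenance prednisolone (protocol 4.8) is 6 × 15 = 90 mg/m². One misjudged date can thus outweigh three study courses (280/90 = 3.1). This shows what a single decision is worth; it does not estimate bias.

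**The case against.** **The ITT statement is about adherence.** SAP 5.3 says "Participants will be analysed in the intervention group to which they were randomised, and all participants shall be included", but the sentence ends by referring to whether the allocated intervention was received. SAP 9.3 says that analysis uses received data in the first instance, and a 12-month total is not observed in a child followed for less. On this reading the completer rule is an available-case rule. That has some force: SAP 5.3 is not breached in plain terms. It does not settle the matter, because dose data that have been received are dropped, SAP 5.5 keeps children with missed visits in the set, and SAP 9.6 already handles partial follow-up for relapse rates.

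**Informative loss is not documented.** Protocol 4.10 keeps children under follow-up after intensification for repeated relapse, and protocol 4.26 does the same for those who stop study drug. This stands. A reader might infer that completer selection understates dose in the control arm and so hides a steroid saving. The documents do not support that: nowhere do they say that leavers relapse more, take more prednisolone or differ by arm.

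**Safeguards exist.** SAP 9.4 provides for cross-checks between forms, use of relapse history for missing dates, and a manual calculation for 20 participants. These constrain the derivation. But the manual check is described as a check of the code, is not said to be blinded, and does not replace a rule for missing dates.

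**The visit window.** A reader might add that a final visit two weeks early loses part of the year. The window is the same in both arms, and SAP 9.4 truncates ongoing doses at randomisation plus 12 months, so this adds nothing of weight.

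**Conclusion.** The point holds as a weakness in how a secondary outcome is defined and derived. The completer set is narrower than the modified ITT set stated for secondary outcomes, it discards received data, and no sensitivity analysis tests it. The judgement steps fall to a statistician who has seen the code; for missing dates and duplicates, that role follows from the general statement at the start of SAP 9.4.

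The outcome is open to bias; the documents do not show that bias occurred, and they do not settle its direction or size. The selection part ranges from zero (equal loss and equal dose gap in both arms) to about 7% of the control mean (8% loss, only control leavers informative, twice the dose rate). The upper figure is a scenario, not an estimate, and reverses in sign if the informative loss is in the active arm. The assessor part cannot be quantified. The primary outcome is not affected, so this is a should-fix.

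**What to change.** **1. Analysis set.** Analyse all modified ITT children whose data may be used. Either take prednisolone dose per unit of observed follow-up, annualised and adjusted for background regimen, or multiply impute the 12-month total. Report the completers' 12-month total as a sensitivity analysis.

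State the weighting. If the 8% of leavers in the working above exit at mid-year, a mean weighted by follow-up time is (0.92 + 0.08 × 0.5 × 2)/(0.92 + 0.08 × 0.5) = 1.00/0.96 = 1.042 against 1.08, so only about half the shortfall is recovered. Equal weight per child would give 0.92 + 0.08 × 2 = 1.08, at the price of unstable rates in children with very short follow-up.

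**2. Derivation.** Before database lock, write down the rules for recoding free text, deleting duplicates and filling dates. Have existing BCTU staff who have not seen the code apply them to an extract without allocation, and freeze the file. Only then merge allocation and add the active-arm study tablets, the one step that needs it.

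**Cost.** Revised wording in SAP 9.4, 9.6 and 9.10, one changed derivation, a masked extract and some staff time; no new data. The downside is an untestable assumption that the observed dose rate, or the imputation model, represents the unobserved time. The completers' analysis should therefore stay in the report.
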